## Discussion

This protocol describes a RCT to be conducted at two hospitals in Bangladesh, aiming to evaluate the effectiveness of integrating an oral health intervention into the MNCH CoC for the prevention of adverse birth outcomes. Specifically, this study investigates whether a combination of basic periodontal treatment (SRP) and the continued use of CHG mouthwash during pregnancy can prevent PTB and LBW. Although the association between oral hygiene and various systemic conditions has garnered increasing attention, the effective oral care methods for preventing adverse birth outcomes remain unclear. Most previous interventional studies have demonstrated that SRP alone is insufficient to significantly reduce the risk of PTB and LBW [29, 30].

At present, strategies to manage periodontal disease during pregnancy and promote oral health care for mothers and children have not been incorporated into the MNCH CoC framework or the World Health Organization’s guidelines for antenatal and postnatal care. In light of the increasing recognition of the importance of maternal oral hygiene, there is a need for a more proactive and sustained approach to oral health. The effectiveness of such an approach may be particularly evident in resource-limited settings, where MNCH indicators remain suboptimal.

This study has some limitations. First, the sample will consist solely of pregnant women in Bangladesh, recruited from two regions (Dhaka and Bogura), which may limit the generalizability of the findings due to potential sampling bias. Second, because of the nature of the intervention, blinding of the dentists performing the baseline dental assessments and the participants will not be feasible. To minimize the risk of assessment bias, endline dental checkups will be performed by independent dentists who were not involved in the baseline dental checkups.

Despite these limitations, demonstrating the effectiveness of this oral health intervention in a real-world setting could provide valuable insights into the potential contribution of oral care to improving MNCH outcomes, particularly in low-resource environments.

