### Randomization and blinding

The trial includes three groups: group A (intervention) and groups B and C (control). All participants will first complete a face-to-face interview at the obstetrics and gynecology department following consent. They will then undergo a baseline dental checkup. Participants diagnosed with periodontal disease will be randomized to group A or B using blocked randomization via computer-generated sequence at each site. Those without periodontal disease will be assigned to group C.

Blinding will be maintained for the interviewers and data recorders, who will not be informed of group allocation. However, blinding will not be feasible for the dentists conducting dental checkups or for participants due to the nature of the intervention.

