#### Dental checkups

Dental checkups (approximately 10 min per participant) will be conducted at both baseline and endline to collect dental data and diagnose periodontal disease [43]. A full-mouth examination will be performed to assess overall oral hygiene status, evaluating the condition of the teeth (sound, carious, treated, or missing), bleeding on probing (BOP), probing pocket depth (PPD), clinical attachment loss (CAL), plaque, calculus, tooth mobility, and oral dryness. BOP is defined as the presence or absence of bleeding during examination of the periodontal pocket. PPD refers to the distance from the gingival margin to the bottom of the pocket, while CAL is the distance from the cemento-enamel junction to the bottom of the pocket [44–46]. Oral dryness will be assessed using a classification scale based on the condition of the tongue mucosa, with higher grades indicating more severe dryness [47].

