##### Diagnosis of periodontal disease

BOP, PPD, and CAL will be measured at six points on each tooth and used to diagnose periodontal diseases, including gingivitis and periodontitis. Gingivitis is diagnosed when BOP is present at 10% or more of the total number of periodontal sites examined. Periodontitis will be diagnosed if either of the following criteria is met: (1) interdental CAL is observed at ≥ 2 non-adjacent teeth, or (2) a buccal or palatal/lingual site exhibits a CAL of ≥ 3 mm and PPD of ≥ 4 mm at ≥ 2 teeth [45, 46].

Participants diagnosed with periodontal disease will be randomized into either the intervention group A or control group B. Participants without periodontal disease will be allocated to control group C.

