### Statistical analyses

The primary analysis will follow the intention-to-treat principle, whereby participants will be analyzed according to their assigned groups, regardless of adherence to CHG mouthwash use during pregnancy. Missing data will be handled using multiple imputation procedures available in the MI suite of Stata. To assess the robustness of the findings, sensitivity analyses will be conducted by comparing results from imputed and non-imputed datasets.

Data from the baseline and endline surveys, dental checkups, and antenatal records will be compared across groups to evaluate the effects of the intervention (SRP combined with CHG mouthwash use) on the primary (PTB) and secondary outcomes (LBW, periodontal disease, and OHRQoL). Initial analyses will include descriptive statistics for participants’ socio-demographic and other basic characteristics, followed by bivariate analyses to examine differences in baseline variables between groups A and B, and between groups B and C.

To estimate the causal effect of the intervention on birth outcomes, comparisons will be made between groups A and B. To investigate whether previously reported associations between periodontal disease and adverse birth outcomes hold in our population, groups B and C will be compared.

For multivariable analyses, two types of regression models will be employed. (1) Multiple regression models will be used to evaluate outcomes measured only at endline. (2) Mixed-effect regression models will be applied for outcomes assessed at both baseline and endline, accounting for potential intra-individual serial correlations in the residual.

Specifically, to assess the effectiveness of the intervention on birth outcomes (PTB and LBW), a multiple regression model will be used, with intervention status (group A or B) as the main predictor, adjusting for potential covariates (socio-demographic characteristics, lifestyle, pregnancy-related characteristics, and pregnancy outcomes). For oral health outcomes (periodontal disease and OHRQoL), mixed-effects regression models will be used, including intervention status (group A or B), time point (baseline or endline), and their interaction terms, while adjusting for potential covariates.

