To evaluate the association between baseline periodontal disease and birth outcomes in groups B and C, a multiple regression model will be employed, with baseline periodontal status (group B or C) as the exposure, adjusting for potential confounders (socio-demographic characteristics and lifestyle at baseline). To assess change in periodontal status between baseline and endline in groups B and C, another multiple regression model will be used with similar covariate adjustments.

To evaluate the association of baseline periodontal diseases and OHRQoL in groups B and C, mixed-effect regression models will be fitted, including baseline periodontal status (group B or C), time point (baseline or endline), and their interaction term, adjusting for the possible confounding factors listed above.

Statistical significance will be set at a *p*-value of < 0.05. All statistical analyses will be conducted using IBM SPSS Statistics version 26.0 (IBM Corp, Armonk, NY, USA) or Stata version 16.0 (StataCorp LLC, College Station, TX, USA).

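### Baseline and endline dental checkups use different dentists, so the planned change in periodontal status (groups B and C) cannot be told apart from a change of examiner, on top of regression to the mean

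*Protocol article*

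**What the plan says.** The limitations paragraph of the Discussion states that "endline dental checkups will be performed by independent dentists who were not involved in the baseline dental checkups". The reason given is "To minimize the risk of assessment bias". It follows from the Randomization and blinding section, which says that "blinding will not be feasible for the dentists conducting dental checkups or for participants due to the nature of the intervention".

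Under Dental checkups, the examinations "will be conducted at both baseline and endline to collect dental data and diagnose periodontal disease". The diagnosis depends on what the examiner reads: "Gingivitis is diagnosed when BOP is present at 10% or more of the total number of periodontal sites examined". Periodontitis is diagnosed from attachment loss and pocket depth. The same baseline reading also forms the groups. Diseased women are randomized to A or B, and "Participants without periodontal disease will be allocated to control group C".

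Two planned analyses use both time points:
- For B and C: "To assess change in periodontal status between baseline and endline in groups B and C, another multiple regression model will be used".
- For A and B, the oral health outcomes get mixed-effects models "including intervention status (group A or B), time point (baseline or endline), and their interaction terms".

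Neither description mentions an examiner effect, and the limitations paragraph does not mention what the switch costs for measuring change.

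**The concern.** Using fresh dentists at endline is a sensible guard against assessment bias. But if no baseline dentist does any endline checkup, every baseline reading comes from one pool and every endline reading from the other. Bleeding, pocket depth and attachment loss all vary by examiner. A pool that probes more lightly or more firmly would look like recovery or progression. This would remain even if the endline dentists were perfectly masked.

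At stake is what the trial may say about untreated periodontal disease in pregnancy (B and C), and any statement that prevalence fell or rose from baseline within a group. Such findings could reflect only who examined the women. Because B and C are defined by a cut-off on the baseline reading, they would also drift towards each other at endline with no change of examiner at all.

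**Working it through.** The plan gives no figure for this analysis. Its sample size concerns preterm birth and is not involved.

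**Step 1: what can be estimated.** Let g be group, t time point (0 baseline, 1 endline) and e examiner pool (0 baseline pool, 1 endline pool):

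E[Y] = b0 + b1·g + b2·t + b3·g·t + d·e

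The Discussion sentence makes e = t for every woman, so E[Y] = b0 + b1·g + (b2 + d)·t + b3·g·t. The design matrix has 5 columns and rank 4, and its null vector loads only on t and e. Only the sum b2 + d can be estimated. The interaction b3 remains estimable.

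**Step 2: inputs for a size.** From the protocol: six sites per tooth and the 10% bleeding cut-off. Assumed, because the documents give no examiner figures:
- 28 teeth, hence 28 × 6 = 168 sites, so the cut-off is 17 or more bleeding sites.
- A true bleeding share that is beta-distributed with mean 0.15 (precision 4), 0.20 (4) or 0.25 (6).
- Binomial readings and no true change.
- An endline pool that records bleeding at r = 1, 0.8 or 1.25 times the baseline pool's rate.

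**Step 3: formulas.** Change in B = −(share of baseline-positive women who read negative at endline). Change in C = +(share of baseline-negative women who read positive at endline). B minus C is the first less the second. By construction B can only fall and C can only rise.

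**Step 4: results** (2,000,000 simulated women per scenario; per cent or percentage points).

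| Mean | r | Prevalence, baseline to endline | B turning healthy | C turning diseased | B minus C change | Shift from r = 1 |
|---|---|---|---|---|---|---|
| 0.15 | 1 | 48.6 to 48.6 | 7.0 | 6.6 | -13.6 | – |
| 0.15 | 0.8 | 48.6 to 42.6 | 15.0 | 2.6 | -17.6 | -4.0 |
| 0.15 | 1.25 | 48.6 to 54.2 | 2.5 | 13.3 | -15.8 | -2.2 |
| 0.20 | 1 | 62.1 to 62.0 | 5.6 | 9.0 | -14.6 | – |
| 0.20 | 0.8 | 62.1 to 55.8 | 12.3 | 3.6 | -15.9 | -1.3 |
| 0.20 | 1.25 | 62.1 to 67.6 | 2.0 | 17.7 | -19.6 | -5.0 |
| 0.25 | 1 | 80.0 to 80.0 | 4.1 | 16.3 | -20.4 | – |
| 0.25 | 0.8 | 80.0 to 73.6 | 9.7 | 6.7 | -16.4 | +4.0 |
| 0.25 | 1.25 | 80.0 to 85.0 | 1.3 | 30.3 | -31.6 | -11.2 |

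The examiner ratio alone moves overall prevalence by about -6 to +6 points. Regression to the mean alone (r = 1) gives a B-minus-C change of -13.6 to -20.4 points. The examiner switch adds between -11.2 and +4.0, in a direction that depends on the unknown ratio.

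**Step 5: sensitivity.** Suppose 43% of women (the periodontitis figure cited in the Background) are positive by attachment loss and pocket depth, independently and stably. Prevalence then moves by about -3.5 points at r = 0.8 and about +3 at r = 1.25, and 5 to 6% of baseline-positive women turn healthy at r = 0.8. In the other direction, a model with noisier readings was run: lognormal bleeding share, median 14%, log-SD 0.7, reading noise log-SD 0.25. It gives a B-minus-C change of -31.5 points with the same pool, and between -29.5 and -44.9 for ratios from 0.7 to 1.3.

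**Step 6: A versus B.** In the lognormal model with no treatment effect, the A-minus-B difference in endline prevalence stays at 0 (to within 0.2 points) at every ratio.

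**The case against.** Five objections deserve weight.

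- The sentence could mean only that no dentist re-examines the same woman. The pools could then overlap and the confounding would be incomplete. The text does not say this, but the sponsor could settle it in a line.
- A reader might infer that no model could ever separate change from examiner. That is too strong. The aliasing holds for a fixed pool effect. If several dentists work in each pool (the number is not given), random effects for individual dentists would leave the time effect estimable but less certain, provided the two pools can be treated as draws from one population.
- A reader might infer that sharing dentists across visits would rescue the B/C comparison. It would not: the r = 1 rows show a change of -14 to -20 points with one pool. Sharing could also weaken the protection of A versus B, since a dentist who knows a woman's treatment might examine her at endline.
- The time term in the A/B model is there to form the interaction. Nothing says that it will be tested as change in disease. This stands, so the point there concerns interpretation only.
- The size rests on assumed ratios and on bleeding alone. This also stands. Attachment loss and pocket depth vary by examiner too, so the smaller shift in Step 5 is illustrative and is not a bound.

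**Conclusion.** The concern holds for the B/C change analysis and for any reading of the time term or of within-group change as change in disease. The confounding needs no numerical assumption, only the plain reading of the Discussion sentence and a fixed difference between pools. Its size is assumption-based: about -6 to +6 points in overall bleeding-based prevalence at ratios 0.8 and 1.25, and probably less if periodontitis by attachment loss and pocket depth is stable. In B versus C, regression to the mean is the larger part in all six shifted scenarios, and the examiner switch adds an amount of unknown sign.

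A reader might go further and infer that the randomized comparison is compromised. The documents do not support that. A and B are randomized within site and both go through the same switch, so a common examiner shift creates no spurious difference at endline or in the interaction. It can change the size of a real effect on the prevalence scale: with A's bleeding assumed to fall to 0.6 times, the lognormal model gives differences from -35 to -20 points across ratios 0.7 to 1.3, while the log-scale effect stays at -0.51. Preterm birth and low birth weight come from antenatal records, and oral-health-related quality of life from interviews, so none of them is touched. This is a problem of moderate weight, confined to secondary periodontal analyses.

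**What to change.** In Statistical analyses:

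- Base conclusions about periodontal status on the randomized A-versus-B contrast, at endline or as the group-by-time interaction. For the binary diagnosis, all women in A and B are positive at baseline by design, so the endline contrast carries the information.
- Do not test or report the time effect, within-group change or B/C change as resolution or progression of disease.
- Present B/C change descriptively only, and state beside it both the examiner switch and regression to the mean.
- Say in the Discussion whether the independence rule applies to the whole pool or to each woman.

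This needs no fieldwork and leaves the primary analysis unchanged. The cost is that one secondary observational analysis loses its inferential status.

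Sharing dentists between baseline and endline is optional. It is acceptable only if each woman's endline examiner did none of her baseline checkup, scaling and root planing or follow-up cleaning, and does not know her group. It would reduce the examiner confounding but not the regression to the mean, so the B/C change would stay descriptive.

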### Trial status

Protocol version 1 (December 2024). Recruitment began on April 27, 2025, and we anticipate concluding the recruitment phase by December 2025. Overall data collection is expected to end in September 2026.

## Data Availability

The datasets used and/or analyzed during the study will be available from the corresponding author on reasonable request.

## Abbreviations

CHG: Chlorhexidine gluconate
CoC: Continuum of care
DQQ: Diet Quality Questionnaire
HFRC: Holy Family Red Crescent Medical College Hospital
LBW: Low birth weight
MNCH: Maternal, Neonatal, and Child Health
OHRQoL: Oral health-related quality of life
PTB: Preterm birth
RCT: Randomized controlled trial
SRP: Scaling and root planing
TMSS: TMSS Medical College & Rafatullah Community Hospital
